1. ***Blinding. [Blinding is used in treatment studies and diagnostic trials to reduce the risk of implementation bias and measurement bias. Implementing strict confidentiality measures, such as using placebos or simulating procedures, is an effective blinding method. If blinding is necessary and feasible for your study, describe the methods and procedures for implementing blinding]***

This trial includes group therapy sessions for students from the same school. As a result, participants may already know each other or be unfamiliar with one another, and they may naturally discuss the experimental training they receive. Maintaining blinding for the researchers is challenging as they may be influenced by the experimental content during the trial. Therefore, meeting the requirements of double-blinding in a clinical trial is not feasible in this situation

1. ***Outcome Measures. [Outcome measures are used to evaluate the results of a study and can include primary, secondary, and safety measures, including adverse events and reactions. Please describe the names of the measures, the methods of measurement, and the time points at which they are assessed]***

As listed in **Table 1**, the primary outcomes include subjective reports of smoking craving, changes in EEG indicators, and mindfulness measures (both trait- and state- mindfulness). The secondary outcomes will be daily smoking behaviours (number of cigarettes smoked per day, exhaled carbon monoxide concentration), affect and impulsivity, as well as indicators reflecting correlation between mindfulness and smoking cue-reactivity. Researchers will inquire daily during the intervention period whether participants experience tobacco withdrawal symptoms or any other adverse reactions. Participants are also encouraged to proactively contact the research team if they experience any adverse reactions. Please refer to item 9 for the time points of assessment.

| **Table 1. Evaluated variables** | | | |
| --- | --- | --- | --- |
| **Variables** | **Timepoints** | **Measures** | **Outcome level** |
| **Category 1: smoking related indices** | | | |
| **Nicotine dependence** | -T1, T0, T1-T5 | **Fagerstrőm test for nicotine dependence (FTND)** is a six-item revision of the Fagerstrőm Tolerance Questionnaire **^[31]^**，scored as 0-3 (low), 4-6 (moderate), and 7-10 (high) with the summed score **^[32]^**. | primary |

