| **Affect** | -T1, T0, T1-T5 | **Positive And Negative Affect Scale（PANAS）**compiled by Watson et al. **^[39]^**, Chinese version **^[40]^** includes 10 corresponding adjectives that described either positive or negative emotion in both the both the negative and positive affect scales. Each project scores 1-5 points, with a total score of 10-50 points. to measure the emotional feelings of the past week. | secondary |
| **VAS for affect** | -T1, T0, T1-T5, during CR task | **Visual analogue scale (VAS)** for affect administered during cue-reactivity experiment to measure the state of affect, including valence and arousal. | secondary |
| **Impulsiveness** | -T1, T0, T1-T5 | **The Barratt Impulsiveness Scale Version 11 (BIS-11)** **^[41]^** was revised in 1995, consisting of a total of 30 items. The revised Chinese version **^[42]^** consists of 30 items, including three dimensions: motor impulsiveness, cognitive impulsiveness, and no planning impulsiveness, with a total score of 30-150, High scores represent hyperactivity, lack of concentration, and lack of planning, respectively. The higher the factor scores of each subscale, the stronger the impulsivity. | secondary |
| **Record of daily practice for mindfulness** | T0, T1 | Self-report of practice time; cognitive, emotional and behavioural states; course feedback and suggestions. | others |
| **Adverse events** | T0, T1-T5 | Proactive reporting without time constraints during research period. | others |
| **Socio-demographic** | -T1 | Age, gender, major, education year, Handedness | others |
| **Handedness** | -T1 | **Edingburgh Handedness Inventory（EHI）**is a measurement scale used to assess the dominance of a person’s right or left hand in everyday activities, sometimes referred to as laterality **^[43]^**, the Chinese version will be used**^[44]^**. | others |
| **Depression** | -T1 | **Patient Health Questionnaire (PHQ-9)** **^[23]^** self-administered tools for assessing depression for recent two weeks, with each project scoring 0-3 points and a total score of 0-27 points, with 6-9 points, 10-14 points, 15-21 points and 22-27 points indicating mild, moderate, severe and extreme severe depression. | others |

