(6) **Participant Suspension:** Participants in this study can request to suspend the intervention. If a suspension is requested, the participant will be evaluated by the study team and, if approved, moved to the future intervention group. Data collected before the suspension will not be included in the final data analysis.

1. ***Definition, identification methods, and management systems for adverse events and reactions.***

In the "Chinese Clinical Smoking Cessation Guidelines," it is stated that smokers may experience a range of withdrawal symptoms after quitting or reducing smoking. These symptoms include smoking cravings, anxiety, depression, restlessness, headache, increased salivary gland secretion, lack of concentration, and sleep disorders. Withdrawal symptoms typically begin within hours of smoking cessation, peak within the first 14 days, and gradually diminish until they disappear. Most withdrawal symptoms last for about one month, although some patients may experience cravings for smoking for over a year.

**Definition:** Adverse events refer to any unfavorable or unintended signs, symptoms, or diseases that occur during or after the intervention, regardless of whether they are related to the intervention. Adverse reactions specifically refer to unfavorable or unintended responses that are causally related to the intervention.

**Identification Methods:** Adverse events and adverse reactions can be identified through various methods, including participant self-reporting, researcher observations, physical examinations, laboratory tests, and medical records.

**Management System:** In light of the potential adverse reactions mentioned above, the researchers will conduct daily inquiries during the intervention to determine whether participants have experienced any of the symptom. The delivered list will also provide information to participants, instructing them to promptly contact the researchers if they experience similar symptoms at any other time. In the event of any adverse reactions, responsible personnel from the medical school and psychology department will promptly contact the participants and assess their psychological and physiological conditions. Based on the participant's willingness, a collective decision will be made by the medical school, psychology department, and participant regarding their continued participation in the subsequent research. The researchers will record the reasons for their decision.

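### After the one-week training, the only adverse-event collection method scheduled at T2-T5 is for participants to come forward themselves

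*Protocol*

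**What the plan says.** Two sections describe active questioning by staff, and both place it in the training period. Outcome Measures says: "Researchers will inquire daily during the intervention period whether participants experience tobacco withdrawal symptoms or any other adverse reactions". The Management System paragraph of the adverse-events section says: "the researchers will conduct daily inquiries during the intervention to determine whether participants have experienced any of the symptom". The randomization section gives the training as one week.

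For other times the protocol relies on the participant. Outcome Measures adds: "Participants are also encouraged to proactively contact the research team if they experience any adverse reactions". The Management System paragraph describes a handout "instructing them to promptly contact the researchers if they experience similar symptoms at any other time". The adverse-events row of Table 1, scheduled at T0 and T1-T5, states its method as "Proactive reporting without time constraints during research period".

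The adverse-events section defines the events to be captured as "any unfavorable or unintended signs, symptoms, or diseases that occur during or after the intervention", whether or not they are related to the intervention. On withdrawal after quitting or cutting down, it says: "Most withdrawal symptoms last for about one month". It also gives general means of identification, "including participant self-reporting, researcher observations, physical examinations, laboratory tests, and medical records", but attaches none of them to a visit.

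**The concern.** The definition of an adverse event covers the period after training, but the scheduled method for that period depends on the participant deciding that something is worth reporting and then making contact. Events that are mild, that have resolved, or that seem unrelated to a smoking study are easily left unreported over long intervals. At stake is how complete the follow-up safety record is. The efficacy analysis is not affected. Participants attend T2-T5 anyway for questionnaires and EEG, so the chance to ask is already there.

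**Working it through.** The protocol states no figure on this point, so the check is a reading of the schedule plus a few counts.

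**1. Who initiates the report in Table 1?** The row does not name the initiator. In Outcome Measures, proactive contact is something participants are encouraged to do ("Participants are also encouraged to proactively contact the research team if they experience any adverse reactions"). The Emergency Team paragraph uses the same word for participants reaching out. The likelier reading of the row is therefore participant-initiated reporting.

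**2. Which visits have a specified adverse-event question?** Daily inquiry covers the training week. T1 follows it directly, so the gap starts after T1.
- Fig 2 note: t2-t5 are follow-ups, 4 visits. Visits with a specified question: 0. Result: 0/4.
- Randomization section: follow-up at 1 week, 1, 3 and 6 months and 1 year, 5 visits. Visits with a specified question: 0. Result: 0/5.

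The two schedules differ, but the answer is the same on either.

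**3. Longest interval between scheduled visits.** Both schedules end with a 6-month and a 1-year visit: 12 - 6 = 6 months.

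**4. What do the repeated scales already cover?** The adverse-events section lists eight withdrawal symptoms. Set against Table 1 at T1-T5:

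| Symptom | Measured at T1-T5? |
| --- | --- |
| Craving | Yes: TCQ-SF, QSU-Brief, VAS |
| Anxiety | Indirectly: PANAS and VAS affect; GAD-7 only at -T1 |
| Depression | Indirectly: PANAS and VAS affect; PHQ-9 only at -T1 |
| Restlessness | At most loosely: BIS-11, an impulsiveness scale |
| Poor concentration | At most loosely: BIS-11 |
| Headache | No |
| Increased salivation | No |
| Sleep disorder | No |

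The count is 1 directly, 2 indirectly, 2 loosely and 3 not at all (1 + 2 + 2 + 3 = 8). Any event outside this list is also not asked about.

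**5. Do the other routes close the gap?**
- General identification methods: Table 1 schedules no physical examination, records review or withdrawal scale at T2-T5.
- EEG sessions: staff stop the recording if the participant reacts badly. This concerns the recording itself and not events since the last visit.
- Contact group and emergency team (Participant management system): both are available to participants, and the emergency team is said to identify affected participants. The only mechanism described is that participants make contact.
- Care after the trial ends: intervention or referral is offered if stress is found to have reached a clinical level. This implies some appraisal, but no instrument is named and Table 1 schedules none for that purpose.

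None of these sets a question about health events since the last contact.

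**The case against.** The strongest case against is that the protocol never says staff will ask only during training. Adverse events are timetabled at T1-T5, when participants meet staff, and the wording of a visit form is often left to a case report form or manual. The programme is a one-week, drug-free behavioural training in volunteers screened for depression and anxiety. Daily questions during exposure, followed by open reporting with support available, can be called proportionate. A definition that includes later events is also compatible with spontaneous reporting, so nothing is strictly contradicted.

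Much of this stands, and it keeps the point minor. It does not remove it, because Table 1 does more than stay silent: it names a method for those visits, and that method is most naturally read as passive.

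A reader might also infer three stronger conclusions that the protocol does not support.
- *That researchers learn nothing about symptoms after week one.* Craving and affect are measured at every follow-up, although as outcomes and not as event records.
- *That safety comparisons between arms will be biased.* The trial is not double-blind, and only the mindfulness arm receives audio for daily practice, so reporting could differ by arm. But adverse events have outcome level others in Table 1, and the statistical section plans no between-arm comparison of them. A difference is possible but speculative.
- *That a large share of withdrawal symptoms will be missed.* The one-month duration applies after quitting or reducing smoking. The trial sets no quit date, so how often withdrawal will occur is unknown.

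**Conclusion.** The point holds as a modest weakness in a stated design choice. On either follow-up schedule, no visit after T1 has a specified adverse-event question, and the longest interval covered by spontaneous reporting alone is 6 months. Three of the eight symptoms that the protocol names, and all other health events, are not asked about in that time. Under-recording is likely, but neither the number of missed events nor any difference between arms can be derived from the protocol. The conclusion assumes that the Table 1 method means participant-initiated reporting, and that no visit form outside this protocol already contains such a question. It is an improvement the team could make and not a necessary correction.

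**What to change.** In the adverse-events row of Table 1, add one short scripted question or checklist at T1-T5, worded and administered identically in both arms. Asking at T1 closes out the training week. It should cover the listed symptoms not already measured (headache, increased salivation, sleep problems). It could also cover those reached only indirectly (anxiety, low mood, restlessness, poor concentration). It should end with an open item on any other health problem since the last contact, and record onset and severity for each event. Keep spontaneous reporting at any time.

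The change takes one table row and a short form at visits already planned. The downsides are a slight extra burden on participants and a higher recorded event count, which the report should attribute to active questioning.

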Nevertheless, the extended time commitment and the need for in-person guidance in traditional mindfulness interventions have resulted in a growing need for shorter, self-practice exercises. According to reports, even single-session mindfulness interventions and brief interventions lasting as little as 5 minutes have shown improvements in health outcomes **^[11, 12]^**. Brief mindfulness interventions have been found to reduce smokers' response to cravings **^[13]^**, improve emotional health **^[14]^**, decrease smoking consumption **^[15]^**, and have been associated with higher rates of abstinence **^[16]^**. Study in natural situation has also demonstrated that brief mindfulness training (BMT) can decrease self-reported negative emotions, smoking cravings, and cigarette consumption **^[17]^**, indicating its effectiveness in smoking cessation treatment.

Furthermore, mindfulness can influence interoceptive processing, potentially regulating brain activity related to cue-reactivity **^[9]^**. Previous research has observed functional changes in interoceptive brain regions **^[18]^**, such as the insula **^[19]^**, as well as control systems including the cingulate gyrus, parietal lobe, and prefrontal cortex **^[20, 21]^** following short-term mindfulness practice. However, there is currently a lack of in-depth research on the regulation of smoking cue responses and related brain mechanisms by brief mindfulness interventions in individuals with TUD.

Therefore, this study aims to explore the intervention effects of BMT on smoking cue-reactivity using a randomized controlled trial design. It seeks to address the limitations of long-duration mindfulness interventions with low acceptance rates among individuals with TUD and provide more targeted intervention strategies by investigating the underlying brain mechanisms. The results of this study will offer valuable insights that can enhance our understanding and support the clinical implementation of short-term mindfulness interventions in addiction treatment.

1. ***Objective***

This study aims to investigate the regulatory effects of BMT on smoking cue-reactivity by integrating subjective reports of smoking cravings with electroencephalography (EEG) data analysis. Additionally, it is dedicated to enhancing our understanding of the underlying brain processes involved and identifying potential EEG biomarkers at various timepoints.

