**Fig 3. Study Design and Procedure**

*The upper portion of the figure illustrates the overall study design. The middle portion depicts the timeline for assessing scales and EEG at baseline, post-intervention, and follow-up timepoints. Brief mindfulness and relaxation training will be administered to both the intervention and control groups after recruitment. The baseline assessment (-T1, T0) will be completed before the intervention. Audio guidance will be provided for daily practice in the BMT group, while there will be no additional practice or intervention for the control group after training. The lower portion of the figure represents the modules of psychological and behavioural assessments during the baseline and five follow-up sessions. The cue-reactivity task will be implemented using a customized two-choice oddball paradigm. INT: intervention, rs-EEG: resting-state EEG; BMT: brief mindfulness training; VAS: Visual analogue scale; SMT: state-mindfulness.*

1. ***Sample size estimation. [List the four elements: δ(Δ) or π1, π2, α, β or Power, and provide the calculation formula]***

In this study, the subjective reports of smoking urges (QSU-Brief) will be used as the primary outcome measure. Referring to study of similar populations **^[28]^**, We set δ(Δ)_tot_ = 4 to represent the anticipated reduction of 4 points in the QSU-Brief score after the intervention in the experimental group. Multiple measurements of the QSU-Brief will be conducted on participants before and after the training, as well as during the 60-minute online training period. To estimate Cohens’d, we have set α = 0.05 and β = 0.80. Cohens’d can be calculated using the formula Cohens’d=(δ(Δ)/SD_estimate_), where the estimated SD_estimate_ was 7.65 based on reference study. Therefore, the corresponding command is pwr.t.test (d=cohens_d, sig.level = 0.05, power = 0.80, type = "paired", alternative = "two.sided"), and the estimated sample size is 34. Therefore, the minimum required sample size for the experimental group is 34. Considering a natural dropout rate of 30%, the sample size for the experimental group should be no less than 45.

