| **Craving** | -T1, T0, T1-T5 | **1.Tobacco Craving Questionnaire-Short Form (TCQ-SF**）is short form of 12 optimized projects to assess smoking craving levels，including four factors of emotionality, expectancy, compulsivity, and purposefulness **^[33]^**, with each factor scores from 3 to 21 points, was used in Chinese population**^[34]^**. | primary |
|  |  | **2.Questionnaire on Smoking Urges-Brief（QSU-Brief）**developed by Cox et al., **^[35]^** suitable for multiple measurements in laboratory and clinical use, including 10 items, can be completed in less than 2 minutes. Each item uses a subjective score of 1-7 points to evaluate the current level of craving for tobacco, the Chinese version will be adopted **^[36]^**. |  |
| **VAS for craving** | -T1, T0, T1-T5, during CR task | **Visual analogue scale (VAS)** administered during cue-reactivity experiment to measure the state of craving, responses to each item were rated using a scale that ranged from 0 (not at all) to 10 (the strongest feeling possible). | primary |
| **Number of cigarettes smoked per day** | -T1, T0, T1-T5 | Self-report for number of cigarettes smoked per day. | secondary |
| **Exhaled carbon monoxide (CO)** | T0, T1-T5 | Instantaneous reading device (Bedfont piCO Smokerlyzer) used to identify whether the duration of cigarette cessation meets the requirements. | secondary |
| **Category 2: mindfulness** | | | |
| **Trait-mindfulness** | T0, T1-T5 | **Five Facet Mindfulness Questionnaire（FFMQ）**consisting of 39 items and 5 factors, namely observation, description, acting with awareness, non-reactivity, and non-judging, the Chinese version will be used**^[37]^**. | primary |
| **State-mindfulness** | T0, T1-T5, during CR task | Based on the Toronto Mindfulness Scale (TMS), two items in Chinese version **^[38]^** were used to evaluate the dimensions of curiosity and decentralization. | primary |
| **Category 3: brain function** | | | |
| **Brain function** | T0, T1-T5 | Using a 64-channel EEG system to record in both resting and experimental conditions. | primary |
| **Category 4: Socio-demographic and clinical information** | | | |
| **Self-emotional assessment** | T0, T1 | **Self-assessment manikin (SAM)** used to measure the emotional state during 7-day mindfulness intervention. | others |

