All data will be analyzed upon completion of data collection. The data analysis process will strictly adhere to the principles of the blind method. Analysis of the data will be conducted using R software (https://www.r-project.org/), IBM SPSS Statistics for Windows, V20.0 (SPSS), MATLAB (MathWorks in Natick, Massachusetts, USA), and EEGlab (https://sccn.ucsd.edu/eeglab). Descriptive statistics will be used for demographic, psychological, and behavioural data at baseline. Two-sample t-tests and χ^2^ tests will be performed for continuous and categorical variables between the intervention group and control group. Repeated measures MANOVA will be adopted to examine intervention effects while adjusting for individual factors and pre-intervention variables (e.g., trait mindfulness and smoking indices). Within-group effects will be investigated through serial trend analysis from -T1 to T5. Linear mixed-effects model analysis will include data from all measures at different timepoints to explore factors associated with smoking cue-reactivity for both groups. EEG data will be preprocessed using Matlab software and the EEGLab toolbox. Relative spectrum power for six EEG bands (delta: 1-4Hz, theta: 4-8Hz, alpha: 8-13Hz, low-beta: 13-20Hz, high-beta: 20-30Hz, and low-gamma: 30-48Hz) will be calculated at the single electrode and ROI level. Microstate and phase synchronization analysis will be conducted, and source localization analysis will be used to investigate functional changes in subcortical brain regions. Repeated measures analysis of variance and simple effect analysis will be performed for EEG indices, considering significance in the professional field. Effect size will be measured using Cohen's d or partial eta-squared values **^[46]^**.

1. ***Participant management system.***

(1) **Contact and Guidance:** A contact group consisting of relevant researchers is responsible for providing guidance and addressing any study-related questions for participants throughout the entire study period. This ensures that participants have a clear understanding of the study and can actively cooperate with the research process. Researchers are required to respond promptly and keep records for participants who withdraw, are excluded, lost to follow-up, terminated, or suspended.

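### EEG change is a primary outcome with no named primary contrast, and its only stated criterion controls no error rate

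*Protocol*

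**What the plan says.** The Outcome Measures section states that "the primary outcomes include subjective reports of smoking craving, changes in EEG indicators, and mindfulness measures", and Table 1 marks brain function as primary, measured at T0 and T1 to T5. The recording is described there as "Using a 64-channel EEG system to record in both resting and experimental conditions". The Objective section adds the aim of "identifying potential EEG biomarkers at various timepoints".

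Under Statistical analysis methods, the first EEG measure is "Relative spectrum power for six EEG bands", which "will be calculated at the single electrode and ROI level". Further families follow: "Microstate and phase synchronization analysis will be conducted, and source localization analysis will be used to investigate functional changes in subcortical brain regions". The test and the criterion then come in one sentence: "Repeated measures analysis of variance and simple effect analysis will be performed for EEG indices, considering significance in the professional field".

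The only numerical significance level in the protocol is in the sample size section, for QSU-Brief: "we have set α = 0.05 and β = 0.80" (the 0.80 is evidently the power). No level is given for EEG.

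**The concern.** A primary outcome should lead to a conclusion whose chance of being wrong under no effect is known. Here the outcome is a large family of indices: six bands, 64 channels plus an unstated number of ROIs, two recording conditions, several visits, and three more types of EEG analysis. No member of the family is singled out in advance.

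The phrase offered as a criterion can be read as convention in the field or as substantive relevance. On either reading it leaves open, until the results are seen, which indices count. At stake is the brain-mechanism conclusion: a reported EEG biomarker could be a chance finding from a wide search, and electrodes or bands picked because they look strong will show inflated effect sizes. Naming QSU-Brief as the sole primary outcome would not cure this, because the search takes place inside the EEG measure.

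**Working it through.** The protocol gives no EEG error rate to reproduce, so the check is how large that rate could be under each plausible reading.

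**Inputs from the protocol.** 64 channels and two recording conditions (Table 1); six bands, calculated at electrode and ROI level (Statistical analysis methods).

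**Assumptions, not in the protocol.** Each EEG test is run at two-sided 0.05. The number of separate tests and the correlations between electrodes and between bands are unknown, so a range is shown.

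**Step 1: independent tests.** With m independent tests, the chance of at least one false positive is 1 − (1 − 0.05)^m.

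| Reading | m | Chance of at least one |
|---|---|---|
| One omnibus test per band, electrode or ROI as a within-subject factor | 6 | 1 − 0.95^6 = 26% |
| The same in both recording conditions | 6 × 2 = 12 | 1 − 0.95^12 = 46% |
| ROI by band, assuming 5 ROIs | 5 × 6 = 30 | 1 − 0.95^30 = 79% |
| Every electrode-band pair, one condition | 64 × 6 = 384 | above 99.99% |

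In the last row, 384 × 0.05 = 19.2 false positives are expected. Positive correlation between the tests lowers the chance of at least one, but not the expected number.

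**Step 2: all 384 pairs with correlation.** Two null simulations with different correlation models were run.

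- *Model A:* 34 per arm (equal arms assumed), two-sample t-test on one change score, electrode correlation decaying with distance, between-band correlation 0.3 or 0.6, 1,500 runs per scenario. Mean electrode correlation 0.66 gives 93% or 86% (the lower figure is for the higher between-band correlation). The stronger of the two other settings, 0.46, gives 99% or 98%. The weaker, 0.22, gives about 100%. The average number of significant tests was 18.1 to 19.9.
- *Model B:* correlated z statistics, between-band correlation 0 to 0.5, 20,000 draws. Equal correlation between all electrodes of 0.5 gives above 99%; 0.7, 94–97%; 0.8, 83–90%; 0.9, 64–75%; 0.95, 49–61%. An 8 × 8 grid with decaying correlation gives 94–97% at mean correlation 0.61 and 79–87% at 0.77.

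The two models agree where they overlap: roughly 86–100% for mean electrode correlation up to about 0.66, falling to about 50% when electrodes are near-duplicates.

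**Step 3: what is left out.** These figures cover band power for one post-baseline change. Microstate, synchronization and source indices, further visits and simple effects all add tests.

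**Step 4: what control would give.** Bonferroni over 384 tests uses 0.05/384 = 0.00013 per test, with a family-wise error of 4.9% if independent. One test per band at 0.05/6 = 0.0083 keeps it at or below 5%. If a 5% family-wise rule is applied separately in each recording condition, the total is 1 − 0.95^2 = 9.75% under independence, so the conditions must be inside the family.

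**The case against.** The strongest reply is that much of the apparent rule is not in the text. The protocol says power is calculated at electrode level; it does not say a separate ANOVA is run at each electrode, and electrode or ROI could enter as a within-subject factor. It sets no EEG alpha and does not say that one significant index counts as a biomarker. The closing clause may mean that practical relevance is weighed alongside the p-value, which would act as an extra filter. The biomarkers are called potential ones, which is the language of candidate-seeking. Multiplicity methods for EEG are also often left to a statistical analysis plan, and none is shown.

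Most of this stands, and it rules out two stronger readings that a reader might infer:

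- *That a false EEG finding is close to certain, with 86% as the floor.* That range needs separate tests of all 384 pairs, 0.05 per test and moderate correlation. None of these is stated, and other readings give 26% or 46%.
- *That the trial cannot tell an effective training from an ineffective one.* That would need an any-hit success rule, which the protocol does not contain. The Study design section frames effectiveness as a reduction in craving, and the sample size rests on QSU-Brief. Neither depends on the EEG search.

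What does not stand is the defence that this is only detail for a later plan. The protocol is not silent: it writes a criterion for a primary outcome, and a statistical analysis plan would have to override that sentence rather than complete it. Nor can EEG be excused as purely exploratory while Table 1 labels it primary. The promise of blinded analysis in the same section guards against favouring an arm, but it does not reduce the number of chance findings.

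**Conclusion.** The point holds in limited form. A primary outcome is left as a large family of EEG indices without a named contrast, and the only criterion is undefined. Assuming 0.05 per test, the chance of at least one false-positive power result under no effect runs from about 26% to near 100%, according to how the ANOVA is organised and how strongly the indices correlate. The 26% and 46% figures assume independent tests; positively correlated bands would bring them down somewhat. The size is therefore conditional, but the absence of error control is not. The consequence is confined to the EEG and biomarker conclusion. The sponsor should correct it before data are seen, which is possible because the Study design section says the trial has not begun.

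**What to change.** Remove the closing clause of the EEG test sentence as a criterion and put a rule in its place:

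1. The primary EEG analysis is the group difference in change of band power from T0 to T1.
2. It is tested with a cluster-based or maximum-statistic permutation test that permutes group labels, at family-wise alpha 0.05 across electrodes, the six bands and both recording conditions. Alternatively, one condition is named as primary in advance and the family covers electrodes and bands within it.
3. Simple effects are run only for effects that pass.
4. Other visits and the microstate, phase synchronization and source results are reported as exploratory.

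Other controlled choices, such as a single pre-named contrast or one test per band at 0.0083, would also meet the point. The cost is a change of wording and a standard permutation routine in the MATLAB and EEGLAB tools already named. The downside is some loss of sensitivity for an effect confined to one electrode. Later visits also become exploratory for EEG, which narrows the stated aim of looking at several timepoints.
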